## Abstract

**Background.** Occupational Performance Coaching (OPC) is a goal-oriented approach in which client agency takes precedence in goal selection, analysis, choice of action, and evaluation of success. The intended outcomes of OPC are improved occupational performance and participation in clients’ life situations. Randomized clinical trials are needed to determine the effectiveness of OPC. **Purpose.** This study protocol outlines a randomized controlled trial (RCT) of OPC compared to usual care with caregivers of children with neurodisability in improving child, caregiver, and family occupational performance. **Method.** A single-blind, 2-arm parallel-group, cluster RCT of OPC compared to usual care is planned. Therapists delivering the intervention (N = 14) are randomized to “OPC training” or “usual care” groups. The primary outcome is occupational performance improvement in caregiver (N = 84) identified goals. **Implications.** Findings will provide translational evidence of the effectiveness of OPC and clarify intervention processes. Areas of future OPC research and development will be indicated.

## Background

Neuro-developmental disability (ND) is an umbrella term describing a range of health conditions (e.g., Autism Spectrum Disorder, Cerebral Palsy, Attention Deficit, and Hyperactivity Disorder) that involve impairment to the developing nervous systems and contribute to functional limitations with onset during childhood (Morris et al., 2013). Disability-related impacts of ND can involve a persons’ physical, cognitive, social, and communication abilities (Morris et al., 2013). Participation in life situations that are valued by children with ND and their families is a key outcome of occupational therapy (Layton, 2017; Restall & Egan, 2021) and the primary intended outcome of Occupational Performance Coaching (OPC: Graham & Ziviani, 2021b).

‘Participation’ involves a person's capacity (e.g., physical or communicative ability), their subjective experience, and the affordance of the environment to support or restrict participation (Imms et al., 2016) Occupational performance and participation are closely related concepts that share a focus on personally valued enactment of societal roles (Graham & Ziviani, 2021b; Imms, 2006). Children with ND are more likely to experience restricted frequency and diversity of participation in comparison with their peers (Imms et al., 2008; Orsmond et al., 2013), discrimination that prevents participation (Huus et al., 2021) and to demonstrate a pattern of decline in participation over time (Majnemer et al., 2015). Interventions are therefore needed that improve the quality of participation experiences for children with ND by addressing the specific abilities and perspectives of the child and family, and the environmental influences on participation. Coaching is proposed as an intervention that can attend to the complex conditions (Novak, 2014) and an alternative to the predominant impairment-oriented interventions in paediatric rehabilitation (Anaby et al., 2017).

A partnership approach is used in coaching to guide clients’ realization of personal priorities (Pentland & Heinz, 2016). In rehabilitation contexts, coaching prompts a shift in focus from what therapists know about clients to how therapists relate to clients in order to amplify client agency. Although there is variation between specific coaching interventions (Kessler & Graham, 2015; Schwellnus et al., 2015), common components include collaborative exploration of future-oriented goals, with an emphasis on client-led reflection, observation, and evaluation of progress (Rush & Sheldon, 2011; Schwellnus et al., 2015).

Coaching of caregivers of children with ND is emerging as a key feature of contemporary evidence-based interventions intending to influence child outcomes (Akhbari Ziegler et al., 2019; Landa, 2018; Missiuna et al., 2012; Novak et al., 2020; Oono et al., 2013). OPC is theoretically grounded in family centred care (Rosenbaum, 1998), the person–environment–occupation model (Law et al., 1996), self-determination theory (Deci & Ryan, 1985), and adult learning theory (Knowles et al., 2005). The family (often in effect the parent/caregiver–child dyad) is the “client.” Client needs for autonomy, relatedness, and competence (Deci & Ryan, 1985) are responded to within the development of a client-directed plan. Clients’ pre-existing knowledge and resources (Knowles et al., 2005) are highlighted and linked to discussions of ways to progress toward goals. Specific OPC components (Collaborative Performance Analysis) guide therapists in prioritizing client knowledge, observation, and reflection over their own expertise, such as knowledge of health conditions and health systems. A logic model for OPC is available (https://www.otago.ac.nz/opc/resources). International (Anaby et al., 2017) and in Aotearoa/New Zealand (Graham et al., 2020; Widdowson et al., 2015) evidence indicates, that while usual care for children with ND is variable, it predominantly reflects directive communication by therapists, infrequent use of goal setting and targeting of children's impairments, thus is substantially different to OPC.

Proof-of-concept that OPC positively influences child, parent, and teacher outcomes has been established in studies conducted in India (N = 36, Angelin et al., 2021), Australia (N = 16, Bernie et al., in press; N = 3, Graham et al., 2010; N = 29, Graham et al., 2013); Hong Kong (N = 4, Chien et al., 2020); Canada (N = 11, Hui et al., 2016) and Germany (N = 3, Kennedy-Behr et al., 2013). Initial randomized controlled trials (RCTs) of OPC with caregivers of children with ND found significant improvement in individualized participation-oriented goals for children with cerebral palsy (N = 43, Jamali et al., 2022; N = 30, Kahjoogh et al., 2019). Both prior RCTs of OPC reflect efficacy study designs in which a single therapist applied OPC within research-oriented recruitment systems. Neither RCT reported intervention fidelity processes that assure that OPC was implemented as intended (Graham & Ziviani, 2021a). While important early steps in the development of evidence, translational research (Woolf, 2008) on OPC is now needed.

The cultural fit of OPC with Māori, the indigenous people of Aotearoa/New Zealand, warrants exploration. Māori are over-represented in many health conditions leading to ND, for example, cerebral palsy and traumatic brain injury. The needs of Māori may be better meet by interventions like OPC that enhance whānau (family) mana (personal authority, status) by promoting active involvement of family, and specific attention to relationship building (whakawhanaungatanga) (Bevan-Brown, 2004; Harwood et al., 2012; Wong et al., 2021). However, Māori caregivers’ experiences of OPC and the need for tailoring of OPC for Māori remain unknown.

### Study Objectives and Hypotheses

The primary objective of this study is to determine if children with ND and their parents /primary caregivers^
1
^ (i.e., child–caregiver dyads) who receive OPC in service delivery contexts, experience improved participation in personally selected life situations compared to usual care. We hypothesise that compared with dyads receiving usual care, dyads receiving OPC will demonstrate greater participation in personally valued life situations as measured by the Canadian Occupational Performance Measure (COPM) (Law et al., 2005).

The secondary objectives of the study are to examine the extent to which implementation of OPC impacts children's functional ability and quality of life, and caregiver mental health; determining if OPC is cost effective compared to usual care; and if outcomes vary according to intervention fidelity and dose. We hypothesise that dyads receiving OPC will demonstrate: (a) greater improvement in child functional ability as measured by the Pediatric Evaluation of Disability Inventory (PEDI-CAT) (Haley et al., 2011), (b) greater quality of life as measured by the KIDSCREEN10, and (c) more positive caregiver mental health as measured by the Depression Anxiety Stress Scale (DASS) (Antony et al., 1998). Previous qualitative (Graham et al., 2010) and quantitative (Chien et al., 2020; Graham et al., 2013) research on OPC have indicated positive effects of OPC on maternal mental health thus indicating this as an important outcome variable in a fully powered analysis of OPC effectiveness. We also hypothesise that OPC intervention is more cost-effective based on COPM outcomes and therapy dosage (session number, length, and frequency).

A further objective is to explore the perspectives of Māori caregivers on the experience of receiving OPC, shared through qualitative interviews. Group differences for Māori in the primary outcome (COPM) will also be analyzed to determine treatment effects for Māori.

### Ethics

Ethical approval has been obtained from [removed for blind peer review] each employer locality and their corresponding Māori consultation committees.

## Method

### Trial Design

This trial (entitled the MANA study: Meaning, Agency and Nurturing Autonomy through OPC) will examine if OPC is superior to usual care using a single-blind, 2-arm parallel group, cluster RCT design, with 1:1 allocation. Clustering will take place at the level of the therapist. See Figure 1 for a flowchart of the MANA study and Supplemental Additional File 1 for the full protocol which has been compiled following the SPIRIT (Standard Protocol Items: Recommendations for Interventional Trials) guidelines (Chan et al., 2013).

**Figure 1. fig1-00084174231160976:**
[figure not shown]
MANA study flowchart. The study population and handling were consistent with the CONsolidated Standards of Reporting Trials (CONSORT).

#### Study Setting and Recruitment

All participants will be recruited from publicly funded Aotearoa/New Zealand community-based rehabilitation services that provide rehabilitation services to children with ND and their families. Each service operates independently, with varying workplace cultures and service processes. Consultations are delivered either in-person or via tele-health.

### Randomization Process

Therapists represent clusters in the study design with study participants defined as caregivers and their children with ND (dyads). After completion of a retrospective case note audit, therapists (N ≥ 14) will be randomized into the OPC or Usual Care groups via a computer-generated randomization sequence, stratified by service (Harris et al., 2009). Thus, services with multiple therapists enlisted in the study will have a mixture of control and intervention group therapists. Therapists in both groups will then each recruit child–caregiver dyads to the study from successive eligible referrals to the service until the total sample size (N = 84) is reached. To enable adequate recruitment of Māori dyads for equal explanatory power for ethnicity, therapists will continue to invite Māori to participate until 42 Māori dyads are recruited (potentially increasing the total sample size to N = 126), or data collection has ended.

### Inclusion and Exclusion Criteria

#### Therapists

Eligible therapists will be registered occupational therapists, physiotherapists, or speech and language therapists, working in publicly funded community rehabilitation services, with a minimum of six months’ experience working with children with ND and their families.

#### Child–Caregiver Dyads

Children and caregivers will be recruited as dyads with the caregiver as the primary intervention recipient. For eligible dyads the caregiver is the primary (or co-primary) caregiver of the child including parents, foster caregivers, whāngai (Māori customary practice when a child is raised by non-birth parents); the child is aged 2–18 (inclusive) with a primary diagnosis of ND, for which the caregiver has sought rehabilitation; the caregiver has one or more goals in relation to themselves, their child or their family, and three or more 1:1 therapy sessions are anticipated by the treating therapist.

The dyad will be ineligible for the study if:
the caregiver lacks sufficient English language skills to complete the outcome measures, because the reliability of measures depends on English language skills,the child has been referred solely for adaptive equipment (e.g., wheelchairs), because equipment prescription is outside the scope of this study,the child or caregiver plan to start an alternative rehabilitation intervention during the study period (e.g., Botox injections) to eliminate potential confounding variables of interventions known to have substantial initial impacts on children's functional ability.

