### Sample Size

The Minimal Clinically Meaningful Difference (MCID) on the COPM is indicated by a change in occupational performance scores of two points on a 10-point scale (Law et al., 2014). A minimum sample size of 46 dyads is required to detect the MCID with 90% power at a two-sided alpha of 0.05, assuming a population standard deviation in COPM scores of two points (Graham et al., 2013). For an ANCOVA analysis of a cluster RCT, this sample size must be multiplied by a design effect to account for the correlation structure of the data (Rutterford et al., 2015). The final sample size has thus been inflated to 84 dyads (spread evenly between 14 or more therapists) to account for clustering (design effect = 1.2), treatment contamination in the control group (20%), and participants lost-to-follow-up (15%). We seek to recruit a minimum of 42 dyads where the caregiver is of Māori ethnicity, to allow for an adequately powered subgroup analysis with 80% power to detect a difference in treatment effect on the COPM.

For post-intervention interviews, 10 Māori who have received a minimum of one high-fidelity OPC session will be successively invited to participate. This sample size is based on prior research (Walker et al., 2017) and will be adjusted according to information power (Braun & Clarke, 2022; Malterud et al., 2016).

In relation to blinding: First, a research fellow (RF), blinded to group allocation, will collect all outcome measures in both intervention and control groups. The RF will have no contact with therapists or access to study data about therapists. Second, dyads will be blind to group allocation. Therapists will not be blinded to group allocation but will be requested not to refer to their group allocation or OPC by name to caregivers and children. Third, the biostatistician will not be blinded however the statistical analysis plan and statistical analysis code will be prepared a priori to the collection of the 16-week outcome data to ensure that analysis processes are not influenced by the data collected.

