#### Occupational Performance Coaching

Therapists trained in OPC are taught to commence by asking questions which guide caregivers to identify their preferred future as goal statements. Goals describe participation in life situations (Imms et al., 2016) and occupational performance (Graham & Ziviani, 2021b). Thus goals in OPC specify observable actions in the context of life situations (i.e., home, school, or community), and reflect the personally meaningful change from caregivers’ perspectives. Therapists learn to move conversations in OPC through a process of Collaborative Performance Analysis from extensive *envisioning* of the preferred future-state goal, *exploring* bridges and barriers to goal progress, and *engaging* caregivers through attention to their psychological needs for autonomy, relatedness, and competence (see Figure 2).

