### Usual Care Group

The comparison group for this study will receive “Usual Care,” which is known to be highly variable in content and dose across Aotearoa/New Zealand (Widdowson et al., 2015), and internationally (Anaby et al., 2017). Although Usual Care as a control group is problematic (Levack et al., 2019), it remains the best choice in this translational study in which OPC effectiveness is being examined with minimal interruption to other aspects of service delivery.

Prior evaluations of usual care in community paediatric rehabilitation in NZ (Graham et al., 2020; Widdowson et al., 2015) indicate: Goal setting is documented about half of the time; goals seldom address changes in participation in life situations, but rather children's impairments and activities; methods vary from hands on (child) to hands off (talking-based) methods and from child-directed to caregiver-directed; discussion with caregivers during intervention ranges from collaborative to directive and advice-based; provision of advice appears to be a dominant model of practice. Each of these features are deviations from OPC processes. Several strategies are in place to enable the description of what occurs within Usual Care and monitor contamination with the OPC group, including analysis of casenotes (OPC-CA), audio recording and coding of treatment sessions (using the OPC-FM), and collection of dose, location and delivery format of sessions. In addition, the sample size estimate has been set conservatively given the expected variation within the Usual Care group. Data will be collected from each Usual Care therapy session until 16 weeks from the initial session.

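### Dyads are recruited after randomization by therapists who know their arm, and one entry criterion is that therapist's own forecast of sessions, so the arms can enrol different families

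*Protocol article*

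**What the plan says.** The Randomization Process section gives the order of events. After a case note audit, "therapists (N ≥ 14) will be randomized into the OPC or Usual Care groups via a computer-generated randomization sequence, stratified by service". Next, "Therapists in both groups will then each recruit child–caregiver dyads to the study from successive eligible referrals to the service". The blinding paragraph under Sample Size states: "Therapists will not be blinded to group allocation but will be requested not to refer to their group allocation or OPC by name".

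Among the entry criteria under Child–Caregiver Dyads, one is that "three or more 1:1 therapy sessions are anticipated by the treating therapist". Another is that "the caregiver has one or more goals in relation to themselves, their child or their family". The first names its judge, the treating therapist. The second names none.

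The blinding measures described are a research fellow who collects all outcomes without knowing the arm, dyads kept unaware of the arm, and an analysis plan and code written before the 16-week data are collected. None of them concerns screening. The Limitations section discusses contamination, variability of usual care and the effect of goal setting, but not differences in who is recruited.

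**The concern.** In a cluster trial, randomizing therapists makes the therapists comparable. It makes their dyads comparable only if dyads are identified before allocation, or by a process that allocation cannot affect. Here the person who delivers the treatment decides, after learning the arm, whether a family is expected to have enough sessions to enter. No bad faith is needed. If training changes how many sessions a therapist expects to give, the same threshold admits a different slice of referrals in each arm.

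If those slices differ in prognosis or motivation, the difference appears as a treatment effect. Analysing dyads as randomized does not help, because the selection takes place before a dyad enters the analysis population. The constrained baseline model in Statistical Methods adds a further dependence. It assumes a common baseline mean in the two arms, which randomization justifies only when recruitment is independent of allocation.

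**Working it through.** **1. The plan's own figures.** Inputs from Sample Size: target difference 2 points, SD 2, two-sided alpha 0.05, power 90%, design effect 1.2, contamination 20%, loss 15%.
- Normal approximation: n per arm = 2 × (1.960 + 1.282)² × 2²/2² = 21.0, so 22 per arm, or 44.
- Noncentral t: power is 89.97% at 22 per arm and 91.2% at 23 per arm, so 46. This agrees with the plan.
- Inflation: 46 × 1.2 / 0.80 / 0.85 = 81.2. The stated 84 equals 14 therapists × 6 dyads. This agrees within rounding.

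The point below changes none of these figures.

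**2. Who applies the criterion, and when.** Side by side, the sections give this order: allocation; training of the OPC therapists; recruitment by therapists of both arms; eligibility that depends on the recruiting therapist's forecast. That training comes before recruitment is implied by the order of the text, not stated outright.

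**3. Size, as an illustration.** The article gives no figure for selection, so these inputs are assumptions: one arm screens out the fraction q = 10–20% of referrals with the poorest outlook, the other arm screens out none, and the judgement correlates r = 0.3–0.5 with the 16-week COPM score.
- Mean shift of the retained group in SD units is φ(z_q)/(1 − q). For q = 10%: 0.1755/0.90 = 0.195. For q = 20%: 0.2800/0.80 = 0.350.
- Shift in COPM points = shift × r × SD. Lowest: 0.195 × 0.3 × 2 = 0.12. Highest: 0.350 × 0.5 × 2 = 0.35.
- Against the 2-point target this is 6% to 18%.
- Standard error: effective number = 84 × 0.85 / 1.2 = 59.5; SE = 2 × √(4/59.5) = 0.519.
- Two-sided rejection with no true effect = Φ(−1.96 + b/SE) + Φ(−1.96 − b/SE). For b = 0.117 it is 5.6%. For b = 0.350 it is 10.4%.

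**4. What baseline adjustment leaves.** Suppose selection shifts COPM by the same amount δ at baseline and at 16 weeks, and the two scores correlate ρ (assumed 0.3–0.7). The bias left after allowing for baseline is about δ × (1 − ρ). For δ = 0.5 this is 0.5 × 0.3 = 0.15 at ρ = 0.7 and 0.5 × 0.7 = 0.35 at ρ = 0.3. Adjustment reduces the bias without removing it. A shift that baseline COPM does not carry at all, such as motivation, is not reduced.

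**The case against.** Four arguments on the other side have weight.

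- **Safeguards exist.** Taking successive eligible referrals limits hand-picking. Stratification by service places both arms in services with several therapists. The additional adjusted analysis covers therapist profession and experience, socio-economic status, ethnicity, education, caregiver mental health, child age and diagnosis. This stands as partial protection. None of it governs who is called eligible, and none reaches unmeasured differences.
- **No shift is shown.** Three sessions is a low threshold, and nothing in the article says that OPC training moves a forecast across it. The objectives ask whether outcomes vary with dose and bring dosage into the cost-effectiveness hypothesis. They do not say that anticipated sessions differ by arm at intake. Families expected to need few sessions might also have the best outlook, so the bias could run either way. All of this stands.
- **The goal criterion is different.** A reader might infer that it has the same fault, because OPC therapists are "taught to commence by asking questions which guide caregivers to identify their preferred future as goal statements", while in usual care "Goal setting is documented about half of the time". The article does not support that. It names no judge for this criterion. The training passage describes delivery, not screening. The usual-care figure concerns documentation by therapists in the past, not whether a caregiver has a goal. The blinded research fellow collects the COPM, with its goal statements, in both arms.
- **The article is condensed.** The full protocol is in a supplement that was not available, and the flowchart is not shown. Screening detail may be there. It would still have to be squared with the printed criterion, which names the treating therapist.

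**Conclusion.** The point holds for the session criterion. An unblinded therapist, after allocation, applies an entry rule that forecasts that therapist's own practice, and no stated safeguard covers this step. The arms can therefore enrol different families.

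A reader might go further and infer that the arms will differ, or that the comparison is tilted towards OPC. The article supports neither. The range of 0.12–0.35 points and 6–10% type I error rests wholly on the assumed selection and correlation. It takes selection in one arm only and makes no allowance for baseline adjustment. Against a 2-point target it is modest. The point is rated as something that should be fixed, because prevention is cheap and analysis cannot fully undo selection once dyads are enrolled.

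**What to change.** 1. Replace the treating therapist's forecast with an arm-neutral criterion, applied to the referral information before the referral is given to a therapist, or by someone unaware of the therapist's arm.
2. Confirm the goal criterion through the blinded research fellow's COPM interview at recruitment (T1). It is already planned in both arms and needs no contact with therapists.
3. Record by arm the numbers of referrals screened, eligible, invited and consented.
4. If the supplement already describes blinded or pre-allocation screening, bring the printed criterion into line with it.

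Cost: amended wording and a short intake form at each service. Some enrolled dyads will have fewer than three sessions. The as-treated sensitivity analysis, which requires two of three fidelity assessments to reach 80%, must say how it classifies them. Referrals need not be redistributed among therapists. That would disturb services that the article describes as independent, in a trial meant to interrupt delivery as little as possible.
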